#### Secondary objectives (Table 1)

**Table 1 Tab1:** Timeline chart of patient clinical evaluation

Outcome measure	Specification	Score	Assessment times				
			Pre-op	Post-op	6w	12w	24w
*Patient-reported outcome measures*							
EQ-5D-3L	General health status	5–15	√		√	√	√
SF-36	General health status	0–100	√		√	√	√
Elderly mobility scale	Fragility Assessment	0–20	√		√	√	√
SARC-F questionnaire	Sarcopenia assessment	0–10	√		√	√	√
NPRS	Joint pain	0–10	√	√	√	√	√
*Hip Joint-specific measures*							
Harris hip score (HHS)	Joint-specific score	0–100	√		√	√	√
Oxford hip score (OHS)	Joint-specific score	0–100	√		√	√	√
*Surgeon and patient related complications*			Intra-op	Post-op	√	√	√
Failure rates				Post-op	√	√	√

*NRPS* numerical pain rating scale, *SF-36* short-form 36, *EMS* elderly mobility scale, *SARC-F* strength, assistance with walking, rising from a chair, climbing stairs, and falls questionnaire, *HHS* Harris hip score, *OHS* Oxford hip score

Several secondary objectives will also be studied to evaluate the effectiveness and safety of the devices by quantifying and drawing presumptions from observed differences between treatment groups in the following:Comparison of perioperative and intraoperative surgical data (age-adjusted Carlson Comorbidity Index [41], operation time, fluoroscopy time and dosage, blood loss, length of hospital stay, prescription of pain-killers, osteoporosis assessment using postoperative DEXA of the unaffected hip, union time and intraoperative surgeon related complications, including lag screw malposition, propagation of the fracture, non-anatomical reduction, varus/valgus deformity, rotational deformity and tip-apex distance-TAD).Pain level at the perioperative period and at 6-, 12-, and 24-weeks postoperatively using the visual analogue scale (VAS) Pain Score.Patient reported general health status prior to surgery and at 6-, 12- and 24-weeks post-surgery using the SF-36 form, the EQ-5D-3L Questionnaire, the SARC-F Index and the Elderly Mobility Scale (EMS).

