#### Patient selection

The patients that will take part in the study, are those over 70 years old, admitted in the Orthopaedic Clinic of the University Hospital of Patras, Greece, suffering from a closed unstable (31A2_1–3_) intertrochanteric fracture. Those patients will be randomized in two groups (Gamma3 and IT). The pre-operative data will be comprised of demographic information, radiological examination of the hips and other questionnaires to conclude the overall physical health and mobility prior the fracture. The participants will be free to withdraw from the study or the investigator can withdraw a patient. If a participant withdraws, they will be listed to a “Change of Status” form and will be invited to present for an endpoint follow-up (Fig. 4).

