#### Randomization

Randomization sequence will be created using Stata 9.0 (StataCorp, College Station, TX) statistical software and will be stratified with a 1:1 allocation ratio using random block sizes of 2, 4, and 6. An investigator not involved in the main study will perform the randomization process. These data will be stored on computer and will be available at the day of the intervention.

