### Statistical analysis

The primary outcome measure of device radiological failure is considered a binary outcome (device failed/did not fail). A binary logistic regression model will be performed to assess the association between the outcome of device failure and the predictor of device type (Gamma3, Intertan). The complication rate of G3 versus InterTan at 24 weeks post-operatively would be compared using a chi-squared (at the 5% level). The differences between HHS and OHS between groups will be assessed using an independent samples *t* test at 24 weeks postoperatively at the 5% level. Test levels, will be adjusted using the methods of Holm-Bonferroni to allow for the multiple comparisons. A linear regression analysis will also be used to quantify the effects of the treatment groups on each of the primary outcome measures, after adjusting for the effects of a range of other important, potentially confounding, factors (e.g. age, gender) recorded for each patient.

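### HHS and OHS are tested with an unadjusted 24-week t test although both scores are collected before surgery; the pre-operative score should be in the Holm-tested model

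*Protocol article*

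**What the plan says.** The clinical Statistical analysis section names the test for the two functional scores: "The differences between HHS and OHS between groups will be assessed using an independent samples" *t* test, and it fixes time and level as a "test at 24 weeks postoperatively at the 5% level". It then says "Test levels, will be adjusted using the methods of Holm-Bonferroni to allow for the multiple comparisons", without listing the outcomes that form the family.

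A second analysis is planned besides the t test: "A linear regression analysis will also be used to quantify the effects of the treatment groups on each of the primary outcome measures". This regression adjusts for an open list of patient factors, of which age and gender are the only examples. The pre-operative HHS or OHS is not mentioned, and no sentence says which of the two analyses decides.

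Table 1 ("Timeline chart of patient clinical evaluation") has four ticks each for HHS and OHS, which read as pre-op and 6, 12 and 24 weeks. Patient selection adds that pre-operative data include "other questionnaires to conclude the overall physical health and mobility prior the fracture". Under Randomization, the sequence "will be stratified with a 1:1 allocation ratio", with the factors not named. The Sample size section rests the trial on these two scores: 78 per group for 90% power, with a fallback of 140 patients in total at 80% power.

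**The concern.** The named test uses one of four scheduled measurements of each score. Function before surgery, or before the fracture, may predict function at 24 weeks. If it does, that part of the between-patient variation could be removed from the treatment comparison at no cost. The t test leaves it in the standard error. If the strata are prognostic, it also ignores the balance that stratified allocation creates, which makes its standard error somewhat too large.

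The planned regression could recover this precision, but as written it need not. Age and gender are its only examples, and nothing restricts the covariates to variables fixed before allocation. The article also records items that arise during or after surgery, such as tip-apex distance, quality of reduction and union time. These can be affected by the nail and should not be adjusted for when estimating its effect.

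At stake is power on the two outcomes that size the trial. It matters most at a Holm-reduced level, or if the fallback sample size is used.

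**Working it through.** **Inputs from the article.** 78 per group, 90% power, 5% level, 1:1 allocation (Sample size; Statistical analysis; Randomization). Fallback: 140 in total including 15% drop-out, 80% power.

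**Assumptions.** Two-sided tests. The correlation r between pre-operative and 24-week score is not given, so 0.2 to 0.6 is shown.

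**Step 1: the effect implied by the plan.** No SD is stated, and the minimum important differences are ranges (HHS 7–10, OHS 5–7), so 78 cannot be rebuilt forwards. Solved backwards with the noncentral t distribution (154 degrees of freedom), 90% power at two-sided 0.05 gives a standardised difference d = 0.522. The noncentrality is 0.522 × √(78/2) = 3.26. The implied SDs are 7/0.522 to 10/0.522 = 13.4–19.2 for HHS and 5/0.522 to 7/0.522 = 9.6–13.4 for OHS.

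Check on the fallback: 140 × 0.85 = 119, about 59 per group. The same d gives 80.3% power at the 5% level, which agrees with the stated 80%.

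**Step 2: effect of adjustment.** ANCOVA on the pre-operative score multiplies the residual variance by 1 − r², so the standardised difference becomes d/√(1 − r²) and 78 per group is worth 78/(1 − r²). The degree of freedom lost is ignored; with 154 it is negligible.

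| r (assumed) | 1 − r² | 78 per group is worth | Power, 5% | Power, 0.025 |
|---|---|---|---|---|
| none (t test) | 1 | 78 | 90.0% | 84.0% |
| 0.2 | 0.96 | 81 | 91.1% | 85.6% |
| 0.3 | 0.91 | 86 | 92.5% | 87.5% |
| 0.4 | 0.84 | 93 | 94.3% | 90.1% |
| 0.5 | 0.75 | 104 | 96.3% | 93.2% |
| 0.6 | 0.64 | 122 | 98.2% | 96.4% |

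The level 0.025 = 0.05/2 is the first Holm step if the family is HHS and OHS. There, adjustment brings power back to 90% at r of about 0.4.

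**Step 3: the fallback, same method.** With 59 per group at the 5% level, power goes from 80.3% to 83.9 / 86.6 / 90.1 / 94.0% for r = 0.3 / 0.4 / 0.5 / 0.6.

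**Step 4: what the 6- and 12-week scores add.** Assume 92 enrolled per group (78/0.85) and the following pattern: 85% with all three visits, 5% with 6 and 12 weeks, 5% with 6 weeks only, 5% with none. Assume a correlation of 0.5–0.7 between neighbouring visits, and 0.9 times that between 6 and 24 weeks. A mixed-model information calculation (normal approximation, d = 0.519) then lowers the variance of the 24-week contrast by 2.7–4.9%. Power rises from 90.1% to 90.8–91.4%, about one point. With the pre-operative score already in the model at r = 0.3, it rises from 92.5% to 93.1–93.6%. Almost all the gain comes from the pre-operative score.

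**The case against.** The strongest reply is that nothing here is wrong. In a 1:1 randomised trial with complete data, a t test on 24-week means is valid, and it matches the stated 24-week aim. That stands: the issue is efficiency only.

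Second, adjustment is already planned, the covariate list is open, and the pre-operative scores are recorded. A full list may be in an analysis plan that is not shown. This stands in part. The article cannot be called purely unadjusted, and it does not rank the two analyses. But it does name the test and attach the 5% level to it, while the regression is introduced as an addition meant to quantify effects. One analysis has to be named as deciding.

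Third, r may be low. A pre-operative score in a patient with an acute fracture is either taken on the broken hip or recalled from before it, and non-ambulatory patients are excluded, which narrows the range. This stands: at r = 0.2 the gain is only one to two points.

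Two stronger readings are tempting. A reader might infer that the t test leaves the trial at about 80% power and that adjustment restores 90%. The 80% requires a three-outcome Holm family tested at 0.0167, which the article does not define; at its stated 5% level, 78 per group has 90%. A reader might also infer that only 24-week completers will be analysed and that a mixed model would repair this at no cost. The article is silent on handling of missing scores, and withdrawn patients are invited to an endpoint follow-up. A model assuming data missing at random would in effect extrapolate 24-week scores for patients who died, so it does not settle how deaths count.

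**Conclusion.** The point holds as a weakness of efficiency. The named test for the two scores that size the trial omits a pre-operative measurement that the trial collects, and the accompanying regression neither names that measurement nor is declared decisive. At 78 per group the gain in power is between 1.1 and 8.2 percentage points at the 5% level, and between 1.6 and 12.4 points at 0.025, for r from 0.2 to 0.6. These figures rest on d = 0.522 implied by the stated power, on two-sided tests, on a two-score Holm family for the 0.025 column, and on an assumed r. If the pre-operative score predicts weakly, the gain is small. The documents do not support calling the t test invalid or biased, nor presenting the earlier follow-up scores as a large source of lost power.

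**What to change.** State in the Statistical analysis section that the Holm-tested analysis of each score is a linear regression (ANCOVA) of the 24-week score on treatment, the pre-operative value of the same score and the randomisation strata, and name those strata. Limit any further covariates to variables fixed before randomisation, and list them. Keep the independent-samples t test as a sensitivity analysis.

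A mixed model that also uses the 6- and 12-week scores can be added as an optional sensitivity analysis for missing data. Its handling of deaths would have to be stated separately.

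The cost is a change of wording before outcomes are seen, and one degree of freedom per covariate. No new data and no extra patients are needed.

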## Discussion

Since the 1960s, the DHS has become the standard implant for surgical treatment of stable intertrochanteric fractures as it allows controlled fracture compression but despite additional modifications, such as trochanteric support plates and antirotational screws, unstable trochanteric fractures are less successfully treated by this method [17–20]. Cephalomedullary nails can provide better lateral wall support in more complex fracture patterns but nevertheless, cut-out of the hip screw has been described as the most frequent mechanical failure for all implants [21–23]. Several studies have shown that the incidence of cut-out for different compression hip screws and cephalomedullary nails ranges from 0 to 16.5% [24–26]. In a recent study by Bojan et al. [27] the primary cut-out rate of Gamma-nail in 3066 consecutive patients was 1.85% and was strongly associated either with unstable fractures involving the trochanteric and cervical regions or the combination of both, non-anatomical reduction and non-optimal screw position which are the only two factors that can be controlled by the surgeon. Recent developments including locking plates, antirotational screws and cement-augmented fixation techniques indicate that the problem of fixation failure is still unresolved [28–31].

The Trigen Intertan (IT) nail (Smith and Nephew) is a current generation IM device, featuring a configuration comprised of a larger superior lag screw and a smaller integrated screw that allows for linear compression of the fragments at the fracture site while providing high rotational stability [32, 33]. Clinical studies evaluating the IT nail against other single screw intramedullary or extramedullary devices have shown controversial results, either similar regarding Harris Hip Score, operation time, blood loss, time to union, mean hospital stay, union problems and perioperative complications [43, 44], inferior, comparing surgical time, blood loss, fluoroscopy usage and intraoperative complications [45–47], or superior in terms of implant failure, mal-union, lag screw cut-out, short term reduction of pain, functional outcomes and uncontrolled varus fracture collapse [33, 48–50].

The aim of this study is to perform a comparative biomechanical testing between a commonly used single screw cephalomedullary nail (Gamma3) and an integrated dual lag screw nail (InterTan) in unstable (AO A2_1–3_) intertrochanteric fractures created on osteoporotic composite femurs. We would hypothesize that the InterTan nail would provide higher stiffness and load to failure and less varus collapse in unstable intertrochanteric fractures after cycling loading. Finite element parametric models of different screw positioning in both implants would be probably reveal the reasons for early or late mechanical complications and implant failures. A prospective, randomized, 2-arm, parallel clinical study will follow including approximately 200 patients. The primary aim would be the differences in radiological measurements (cut-out, varus displacement, loss of reduction, malunion, nonunion) between Gamma3 and IT in closed unstable intertrochanteric fractures (AO A2_1–3_) in patients aged over 70 years old at the 24-week follow-up evaluation. The second primary aim would be the functional status at the 24-week follow-up using patient reported disease-specific scores (HHS and OHS) along with several other perioperative and postoperative data, level of pain and general health status (SF-36, EQ-5D-3L, SARC-F Index and Elderly Mobility Scale).

Recent systematic reviews and metanalyses have reported controversial results regarding the superiority of InterTan to other single or double lag crew cephalomedullary nailing systems. Ma et al. [13] demonstrated that IT was not found to be superior to 1-screw nailing system (Gamma3, PFNA) in terms of Harris Hip Score (HHS), blood loss, total complications, union time, length of hospital stay, revision rate, and fluoroscopy time; in contrast IT showed less implant cut-out rate and femoral fractures when compared with the control groups. The authors concluded that since IT shows similar functional recovery, revision rate and longer surgery time, it is not worthy of being recommended as an alternative intramedullary nail in intertrochanteric fractures.

Nerhera et al. [51] found that InterTan was clinically more effective when compared to a single screw cephalomedullary nail (PFNA) resulting in fewer complications, fewer revisions and fewer patients complaining of pain. No difference has been established regarding non-unions and Harris Hip Score. Intraoperative outcomes favour PFNA with less blood loss and fluoroscopy usage. The authors concluded that further studies are warranted to explore the cost-effectiveness of these and other implants in managing patients with intertrochanteric fractures.

Date et al. [52] showed that PFNA and Gamma3 had better intraoperative outcomes compared with IT; however, IT had superior implant-related outcomes of cut-out and screw migration. No difference was found between IT and PFNA or Gamma3 in Harris Hip Scores, time to union, malunion and nonunion. The authors suggested that further long-term studies are needed to evaluate clinical outcomes and cost–effectiveness of these cephalomedullary devices.

Onggo et al. [53], reported that InterTan was associated with lower complication rates in terms of all-cause revisions, cut-outs, medial or lateral screw as well as persistent hip and thigh pain. In terms of perioperative parameters, InterTan was associated with longer operative and fluoroscopy times. There was no statistically significant difference in terms of clinical Harris Hip Score and radiological outcomes, non-union, haematoma, femoral fractures, varus collapse, length of stay and mean intraoperative blood loss between the 2 groups. The authors concluded that integrated dual lag screw cephalomedullary nails are associated with fewer revisions and complications but there is insufficient data to suggest that either nail construct is associated with better functional outcomes.

Finally, Quartley et al. [54] in their recent metanalysis of 23 studies (17 with unstable fractures) found that IntetTan reduced the risk of revision/reoperation by 64%, implant failures by 62% and hip and thigh pain by 50% in unstable fractures. No differences were noted between IM nail designs for infection rates, healing time, non-union rates, femoral shortening, or Harris Hip Score. The authors concluded that IT nail may reduce incidence of implant-related complications, hip and thigh pain, and the need for revision/reoperation without compromising clinical and functional outcomes.

### Limitations

Our study has several limitations. Firstly, the surgery will be performed by several orthopedic surgeons of our department that have different surgical experience, but they all were trained at the same hospital and the reduction will be closed monitored to be as anatomical as possible. Second, the assessment of fracture healing, cut-out, varus displacement and other complications will be measured with digitalized radiographs that can be misinterpreted by wrong patient positioning and intraobserver variability. Third, there are many factors contributing to fracture healing and regain of functional status that are mostly patient depended, especially in these fragile population of > 70 years old. The main weaknesses of the biomechanical study are its static nature and uniplanar loading configuration. Mechanical failure is a dynamic event in clinical practice, and rotational displacement is equally important to frontal plane displacement postoperatively. However, the current study will test the initial loading characteristics of various lag screw(s) configurations at subcritical stress levels and can serve both as a guide at events at early postoperative ambulation status and as a reference for future dynamic studies with more complex loading characteristics.

## Conclusions

Despite recent advances in the treatment of intertrochanteric fractures, the surgeon related parameters (type of reduction, implant selection and optimal surgical technique) remain the most important factors for a successful clinical and radiological outcome. Taking into consideration the increased health risks related to the treatment of mechanical complications alongside the increased hospitalization and health care costs in the setting of an aging European population, the need to improve treatment outcomes of these fractures is evident. This entails both enhancing our understanding of the prognostic factors of mechanical failure and improving all aspects of intertrochanteric fracture treatment through the optimization of the biomechanical behavior of the fracture-osteosynthesis model by the application of the ideal reduction angle and implant; this is expected to have a positive effect on the rate of mechanical failure and, subsequently, the healing rates, morbidity, and mortality in this fragile patient group.

## Data Availability

The primary investigators are responsible for data storage and availability upon request.
